**Sao Paulo-SP**

**2019**

**ABSTRACT**

Halitosis is a term that defines any odor or bad smell originating from the oral cavity, which may have local or systemic origin. This project aims to verify whether the treatment with antimicrobial photodynamic therapy (aPDT) and the treatment with the use of probiotics are effective against it. Fifty-two UNINOVE students or employees, aged between 18 and 25 years old, with a diagnosis of halitosis, showing sulfhydride (SH2) ≥ 112 ppb on gas chromatography will be selected. Participants will be randomly divided into 4 groups of 13, which will receive different treatments: Group 1: treatment with brushing, dental floss and tongue scraper; Group 2: brushing, flossing and aPDT applied to the dorsum and middle third of the tongue; Group 3: floss brushing and probiotics; Group 4: brushing, flossing, aPDT and probiotics. The results of halimetry will be compared before, immediately after treatment, seven days after and thirty days after treatment. A microbiological analysis of the tongue coating will be carried out at these same times. Quantitative analysis will be performed using real-time PCR. Data normality will be checked using the Shapiro-Wilk test, and, in the case of normality, the Analysis of Variance (ANOVA) test will be applied, and, in the case of non-parametric data, the Kruskal-Wallis test will be used. To analyze the results of each treatment in the two study periods, the Wilcoxon test will be used.

**Descriptors:** Halitosis, Photodynamic Therapy, Bixa orellana, Probiotics

**Clinical Trials:** NCT03996044

**1. INTRODUCTION**

Halitosis is a term that defines any odor or bad smell from the oral cavity, which may have a local or systemic origin [1].

Volatile Sulfur Compounds (CVS) are chemical components that are related to halitosis, they are: hydrogen sulfide (H2S), methylmercaptans (CH3SH) and dimethylsulfide (CH3SCH3) [2-5].

There are different methods for diagnosing halitosis: clinical evaluation, known as an organoleptic test, a subjective method that consists of feeling the smell exhaled through the mouth and nose, and then quantifying this odor using a scale. CVS can be measured using sulfide monitors. And gas chromatography is the most appropriate method for diagnosing halitosis of any origin, as it measures the 3 main sulfide gases, methylmercaptan and dimethylsulfide [6-8]. Despite having a complex etiology, anaerobic bacteria are identified as the main cause [6]. The prevalence of halitosis is high, and it is possible to find values above 50% in the literature [9].

Conventional treatments used to control halitosis basically consist of the use of dentifrices and mouthwashes containing bactericidal substances, use of a lingual scraper, treatment of caries lesions and periodontal disease, in addition to controlling xerostomia [10]. Some studies suggest that amine fluoride has a positive effect in reducing halitosis [9].

Studies show that alternative treatments such as Antimicrobial Photodynamic Therapy (aPDT) [12, 13, 14] and probiotics have been used in an attempt to control halitosis [9, 10, 15].

aPDT is a treatment in which a photosensitizing agent is used that, in the presence of light, produces oxygen free radicals leading to cell death [16].

Probiotics are defined as microorganisms that provide beneficial effects to the health of the host when absorbed by it. They are often used in food and fermented products, in addition to being used in pharmaceutical manipulations [17].

Advantages of alternative approaches are reduced tissue damage and avoidance of bacterial resistance.

**2. JUSTIFICATION**

Halitosis is considered an important social factor, as it interferes with interpersonal relationships. In addition to generating concerns related to the physical health of the individual, it can cause psychological changes, leading to a social barrier [18].

The realization of the project is justified due to the scarcity of studies that evaluate the reduction of halitosis through photodynamic therapy and the use of probiotics, presenting annatto as a photosensitizer and LED as a more accessible light source for dentists. Although methylene blue combined with red laser has already been used for this purpose, this study will evaluate the effect of aPDT with annatto and LED to reduce halitosis. The fact that annatto is red facilitates the work combined with a light emitting diode (LED) and allows its use on a larger scale. In addition, the LED is low cost and most dentists already have the device in their offices. Protocols with the use of LED to reduce halitosis have already been developed and obtained positive results, observing recolonization after 7 days of treatment [12, 19]. The purpose of this project is to continue these protocols, adding the use of probiotics and analysis by gas chromatography up to 30 days after treatment to assess its effectiveness.

The use of probiotics in dentistry presents an innovative treatment, capable of modifying the oral microbiota, especially with regard to halitosis, since the oral microbiota is complex and a major challenge in the development of protocols for the prevention and treatment of the disease [20] .

The present study proposes a controlled clinical trial to compare the effect of photodynamic therapy and the use of probiotics in controlling halitosis.

**3. HYPOTHESIS**

*Experimental hypothesis:* There is a decrease in halitosis after the use of photodynamic therapy using blue dye and red LED. There is a decrease in halitosis after treatment with probiotics. There is microbiological change after antimicrobial photodynamic therapy. There is microbiological change after treatment with probiotics.

*Null hypothesis:* There is no change in halitosis after the use of photodynamic therapy employing the use of blue dye and red LED. There is no change in halitosis after treatment with probiotics There is no microbiological change after antimicrobial photodynamic therapy. There is no microbiological change after treatment with probiotics.

**4. OBJECTIVE**

The objective of the present study is to verify if the treatment with aPDT, using annatto as a photosensitizer and the LED as a light source, is effective in the immediate reduction of halitosis when evaluated by gas chromatography, as well as to compare this method with the use of a tongue scraper, most commonly used conventional method, use of dental floss and brushing with amine fluoride toothpaste (Elmex®) and use of probiotics.

Perform a quantitative microbiological analysis of the bacteria present on the tongue coating before and after treatment, using real-time PCR.

**5. MATERIAL AND METHODS**

An invitation will be made and participants who are interested in participating will be selected. 52 students or employees of UNINOVE with a diagnosis of halitosis, showing sulfhydride (SH2) ≥ 112 ppb in the gas chromatography will be included. Participants will be divided through block randomization into four groups (n=13), according to the treatment to be performed (Figure 1). Group 1: treatment with brushing, dental floss and tongue scraper; Group 2: brushing, flossing and aPDT applied to the dorsum and middle third of the tongue; Group 3: floss brushing and probiotics; Group 4: brushing, flossing, aPDT and probiotics. The results of halimetry will be compared before, immediately after treatment, seven days after and thirty days after treatment. A microbiological analysis of the tongue coating will be carried out at these same times. Quantitative analysis will be performed using real-time PCR. This work will be sent to the Research Ethics Committee of UNINOVE and because it is a randomized clinical trial and seeking greater transparency and quality of this research, we will use the recommendations of CONSORT (Consolidated Standards of Reporting Trials)

**5.1. Inclusion criteria**

Participants of both genders, aged 18 to 25 years, with a diagnosis of halitosis showing sulfhydride (SH2) ≥ 112 ppb in gas chromatography will be included in this research.

**5.2. Exclusion Criteria**

Individuals with dentofacial anomalies (such as cleft lip, palatine and nasopalatine fissures), undergoing orthodontic and/or orthopedic treatment, undergoing oncological treatment, with systemic alterations (gastrointestinal, renal, hepatic), under antibiotic treatment up to 1 day will be excluded from the study. month before the survey and pregnant women.

**Randomization**

Randomization will be performed using the randomizer.org website and the order will be placed in a brown envelope and the participant will remove the envelope at the time of treatment.

**Procedures**

Because it is a randomized clinical trial and seeking greater transparency and quality of this research, we will use the CONSORT recommendations (Consolidated Standards of Reporting Trials) (figure 1).

**Individuals from the UNINOVE dental clinic**

**Excluded**

**Recruitment**

**Halimetry**

**Excluded SH2<112ppb**

**SH2 diagnosis>112ppb**

**n=52**

**Group4**

**n=13**

**Group 3**

**n=13**

**Group 2**

**n=13**

**Group 1**

**n=13**

**Brushing, flossing and aPDT e probiotics**

**Brushing, flossing and probiotics**

**Brushing, flossing and scraper**

**Brushing, flossing and aPDT**

**New halimetry immediately after treatment**

**Halimetry after 7 days**

**Halimetry after 30 days**

**Analysis of results**

**Figure 1:** Flowchart of activities.

**6. INTERVENTIONS**

**Group 1 - Brushing, flossing and scraper**

1- Initial measurement

2- Collection of lingual coating with swab

3- Tongue scraping

4- Oral Hygiene Guidelines

5- Halimetry immediately after scraping

6- Halimetry after 7 and 30 days

**Group 2 – Brushing, flossing and aPDT**

1- Initial measurement

2- Collection of lingual coating with swab

3- Application of annatto spray on the back of the tongue for 2 minutes

4- Application of LED in 6 points

5- Oral Hygiene Guidelines

6- Halimetry immediately after aPDT

7- Halimetry after 7 and 30 days

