The collection of oral air will follow the manufacturer's guidelines (Oral ChromaTM Manual Instruction), where the participant will be instructed to rinse their mouth with cysteine (10 mM) for 1 minute, then remain with their mouth closed for another 1 minute. A syringe from the same manufacturer designed to collect mouth air will be introduced into the participant's mouth. For 1 minute, the participant will remain with his mouth closed, breathing through his nose, without touching the syringe with his tongue. The plunger will be pulled out, we will again empty the syringe into the participant's mouth and again we will pull the plunger to fill the syringe with the breath sample. We will clean the tip of the syringe with gauze to remove moisture from the saliva, place the gas injection needle on the syringe, and adjust the plunger to 0.5 ml. The collected gases are injected into the inlet port of the device with a single movement (Figure 4).

**Figure 4:** Process of carrying out the halimetry.

From the analysis of the VSCs captured by the system, we have:

- Sulfidride: origin mainly from the bacteria present on the back of the tongue. Values above 112 ppb are indicators of halitosis.

- Methylmercaptan: predominantly higher in periodontal pockets. Values up to 26 ppb are considered normal. Periodontal disease typically results in a high methylmercaptan/sulfhydride ratio (>3:1)

- Dimethylsulfide: it can either be of periodontal or systemic origin (intestinal, hepatic, pulmonary). It can also be temporarily caused by eating certain foods and drinks. It is possible to distinguish between dimethylsulfide of oral origin and that of systemic origin, by comparing the results of halimetry with and without the cysteine challenge (cysteine 10 mM, i.e., 16 mg of cysteine in 100 ml of water distilled – 16 mg%). The perception threshold for dimethylsulfide is the lowest, 8 ppb. Other odors (not VSCs) may appear in a peak prior to the theoretically first peak, which is the sulfhydride.

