The lingual coating samples will be collected using 1 sterile swab that will be passed on the surface of the dorsum of the tongue with a back and forth movement 10 times. The samples will be deposited in sterile tubes that will be identified and stored at -80 C until they are analyzed. After thawing, the samples will be submitted to the vortex for 1 minute. For bacterial DNA extraction, the samples will be submitted to a boiling bath for 10 minutes and then centrifuged at 10,000 rpm for 10 minutes. The supernatant will be placed in a new microtube containing 100μL of phenol/chloroform/isoamyl alcohol (25:24:1), followed by ethanol precipitation. Purified DNA will be resuspended in TE buffer. The levels of P. gingivalis, T. forsythia and T. denticola will be analyzed by quantitative PCR. Quantitative analysis will be performed by real-time PCR using a Step One Plus Real-Time PCR System thermal cycler (Applied Biosystem, Foster City, CA, USA) and the products detected by fluorescence using the Quantimix Easy SYG Kit (Biotools, Madrid, Spain), following the protocol recommended by the manufacturer. For the reaction will be used 10 µl of SYBR Green, 0.5 µl template DNA, 200 mM of each primer (P.gingivalis CATAGATATCACGAGGAACTCCGA TT and AAACTGTTAGCAACTACCGATGTGG; T.forsythia GGGTGAGTAACGCGTATGTAACCT and ACCCATCCGCAACCAATAAA; T. denticola CGTTCCTGGGCCTTGTACA and TAGCG ACTTCAGGTACCCTCG; Universal for bacteria CCATGAAGTCGGAATCGCTAG and GCTTGACGGGCGGTGT) in a total volume of 20 µl. For the standard curve, reactions containing as template DNA 2 to 2X105 copies of the analyzed gene (16S rRNA) will be performed using pTOPO plasmids in which the 16S genes of 14 different organisms will be cloned. As a negative control, sterile milliQ water will be added instead of template DNA. Reactions for 16S rRNA will be performed with initial denaturation at 95°C for 2 minutes, followed by 36 cycles of 94°C for 30 seconds, 55°C for 1 minute and 72°C for 2 minutes and final extension at 72°C for 10 minutes 46. Fluorescence will be detected after each cycle and graphed using Step One Plus Real-Time PCR System software (Applied Biosystem, Foster City, CA, USA). To ensure the specificity of products detected by fluorescence and to avoid detection of primer dimers, detection will be performed one degree below the dissociation temperature of the amplicons. All samples will be analyzed in duplicate and each plasmid dilution for the standard curve in triplicate. The purpose of the microbiological evaluation will be to verify the effectiveness of photodynamic therapy for the treatment of halitosis, complementing the clinical evaluation.

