
*Antimicrobial Photodynamic Therapy (aPDT)*

An LED light curing device – Valo Cordless Ultradent® will be used, an office device with coupled radiometer, spectrum of 440-480nm and irradiance of 450mW/cm. At the time of performing the aPDT, only the participant to be treated and the responsible professional will be present, both wearing specific glasses for eye protection. The active LED tip will be coated with disposable transparent plastic (PVC) (avoiding cross-contamination and for hygiene reasons) and the professional will be properly dressed.

1 aPDT session will be performed with the photosensitizer (FS) annatto manipulated at a concentration of 20% (Formula e Ação®) in spray, to be applied in sufficient quantity to cover the middle third and dorsum of the tongue (5 sprays) for 2 minutes to incubation. The excess will be removed with a sucker in order to keep the surface moist with the FS itself, without using water. Six points will be irradiated with a distance of 1 cm between the points, considering the halo of light scattering and effectiveness of aPDT. The apparatus will be previously calibrated with a wavelength of 395-480 nm, for 20 seconds per point, energy of 9.6J, and the light will be irradiated so that a halo of 2 cm in diameter per point is formed. Table 1 contains all parameters used.

Table 1: LED parameters.

| Wave-length (nm) | 395-480 |
| --- | --- |
| Operating mode | Contínuo |
| Average radiant power (mW) | 480 |
| Polarization | aleatória |
| opening diameter (cm) | 0.9 |
| Irradiance at aperture (mW/cm2) | 762 |
| Beam profile | Top hat |
| irradiated area (cm2) | 3.14 |
| target irradiance (mW/cm2) | 153 |
| Exposition time (s) | 20 |
| Fluency (J/cm2) | 6.37 |
| radiant energy (J) | 9.6 |
| Number of irradiated points | 6 |
| total irradiated area (cm2) | 18.8 |
| Number of sessions | 1 |
| total radiant energy (J) | 57.6 |

*Tongue scraping*

The lingual scraping will be performed by the same operator in all participants. Posterior-anterior movements will be performed with the scraper on the lingual dorsum, followed by cleaning the scraper with gauze. This procedure will be performed ten times in each participant, with the aim of standardizing the mechanical removal of the tongue coating.

*Treatment with probiotics*

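### In Groups 1 and 2 the tongue is swabbed between the initial and the immediate halimetry, so the within-group immediate change mixes coating removed by sampling with the treatment effect

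*Protocol*

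**What the plan says.** The Objective section of the protocol asks first whether aPDT "is effective in the immediate reduction of halitosis", judged by gas chromatography, and then compares aPDT with the tongue scraper and the other treatments.

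Section 6 gives the order of procedures. In Group 2 the initial measurement is followed by "2- Collection of lingual coating with swab", the annatto spray, the LED, hygiene guidance and "6- Halimetry immediately after aPDT". In Group 1 the swab is also the second step. Scraping and hygiene guidance follow, then "5- Halimetry immediately after scraping". Neither list has a halimetry between the swab and the treatment.

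Under Microbiological analysis, the swab is "passed on the surface of the dorsum of the tongue with a back and forth movement 10 times". Under Tongue scraping, the Group 1 intervention is drawn over the same surface: "This procedure will be performed ten times in each participant, with the aim of standardizing the mechanical removal of the tongue coating". Under Halimetry, the protocol names where the measured gas comes from: "Sulfidride: origin mainly from the bacteria present on the back of the tongue".

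Under Statistical analysis, groups are compared by ANOVA or Kruskal-Wallis with post-hoc tests. Each treatment's change between two study periods is tested by a paired t test or a Wilcoxon test.

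**The concern.** The swab exists to lift coating off the tongue, and the protocol treats mechanical removal of coating from that surface as an active treatment. A before-to-immediate fall in sulfhydride within Group 2 can therefore come from the aPDT, from the sampling, or from both. No listed reading separates them: there is none after the swab and before treatment, and no arm is swabbed, left untreated and measured at once.

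What is at stake is the within-group evidence for the first objective. Groups 3 and 4 are also swabbed after their initial measurement, but their next listed halimetry is on day 14. On the listed procedures, Group 2 is therefore the only aPDT arm with a same-visit reading. If its paired test is significant, part of the fall may be a by-product of taking the microbiological sample.

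**Working it through.** **Inputs.** The order of steps is from Section 6, Groups 1 and 2. The swab's site and number of passes are from Microbiological analysis, the scraper's from Tongue scraping, and the source of sulfhydride from Halimetry. The 13 participants per group and the two-sided 0.05 level are from Sample calculation. The documents give no figure for the swab's effect, so any size is an assumption.

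**The plan's own figure.** The 13 per group cannot be reproduced, because the means and variances behind the effect size are not stated. This point does not dispute it and uses it only as the number of pairs.

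**What each change contains.** Let s be the fall due to the swab, a the fall due to aPDT and c the fall due to scraping, if all simply add.

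- Group 2, initial to immediate: s + a.
- Group 1, initial to immediate: s + c.
- Group 2 minus Group 1: (s + a) − (s + c) = a − c.

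Each within-group change carries s. The contrast between the two groups does not.

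**If the effects do not add.** Suppose the scraper would in any case have removed part of what the swab took, and call that overlap o.

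- Group 1 changes by s + c − o.
- Group 2 minus Group 1 is (s + a) − (s + c − o) = a − c + o.

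That would favour aPDT, but the documents give no means of judging o.

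**With the swab moved ahead of the baseline reading.**

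- Group 2 changes by a.
- Group 1 changes by c − o.
- Group 2 minus Group 1 is again a − c + o.

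Reordering takes s out of each within-group change and leaves the between-group contrast as it was.

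**Size under assumed values.** Take a treatment with no effect of its own and a swab effect of δ standard deviations of the paired difference. The chance that a two-sided paired t test with n = 13 is significant comes from the noncentral t distribution with 12 degrees of freedom and noncentrality δ√13, where √13 = 3.606.

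| Assumed δ | Noncentrality | Probability of significance |
| --- | --- | --- |
| 0 | 0 | 0.05 |
| 0.25 | 0.90 | 0.13 |
| 0.50 | 1.80 | 0.38 |
| 0.75 | 2.70 | 0.70 |

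For scale, the change that this test detects with 90% power at n = 13 is 0.98 SD. A swab effect of 10%, 25% or 50% of that change gives probabilities of 0.06, 0.13 and 0.37. The distortion is negligible if the swab removes little and material if it removes much.

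**The case against.** The strongest reply is that nothing shows the swab to matter. An equal count of passes does not mean equal removal: one instrument is a scraper used to clear coating and wiped with gauze, the other a single swab used to obtain a sample. This stands. The documents support the direction of the bias, not a large size, and a reader who infers that the immediate fall after aPDT would be mostly a sampling artefact goes beyond them.

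Second, the protocol also plans between-group tests, and Groups 1 and 2 are randomised and swabbed alike. This stands too, for an additive effect. A reader might infer that the comparison of aPDT with scraping is itself biased. That needs the effects not to add, which is possible but not shown, and reordering would not cure it.

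Third, the statistical section does not say which two periods the paired test covers. Reading it as including before versus immediately after is an inference. It is a reasonable one, because Section 5 lists those two time points among the halimetry results to be compared and the objective concerns an immediate reduction.

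Fourth, the within-group change is uncontrolled anyway. Participants are selected on sulfhydride of at least 112 ppb, so regression to the mean could lower the next reading if the first measurement is also the qualifying one. That is correct, but it does not justify leaving in a second source of apparent fall that can be removed.

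A reader might also infer that swabbing would move participants across the 112 ppb cut-off and so create responders. The protocol uses that value for diagnosis and eligibility and plans no responder analysis, so this does not follow.

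**Conclusion.** The concern holds for one quantity: the within-group change from the initial to the immediate halimetry in Groups 1 and 2. As listed, that change combines sampling and treatment and is biased toward an apparent fall. The size is unknown and may be small; the probabilities in the table rest on assumed swab effects. The conclusion also takes the initial measurement in Section 6 to be halimetry.

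It does not extend to the randomised Group 1 versus Group 2 contrast under additivity, to the day-14 readings of Groups 3 and 4, or to days 7 and 30. The change is a cheap improvement to the procedure lists, not a correction on which the trial's validity depends.

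**What to change.** - In Section 6, take the swab before the initial halimetry that serves as the outcome baseline.
- Take any immediate post-treatment swab after the immediate halimetry. The lists do not place the later swabs, although Section 5 plans microbiology at the same times as halimetry, so the order needs stating anyway.
- Keep swab-then-halimetry at later visits in all four groups, so that compared readings follow the same sampling.
- Keep eligibility on the unswabbed screening reading.
- Base the claim of aPDT efficacy at the immediate time point on the randomised between-group contrast, and present the within-group change as descriptive support.

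**Cost.** If the screening halimetry is separate from the first step in Section 6, this only reorders two steps. If they are the same reading, it adds one halimetry per participant after the swab. Figure 1 and Section 6 do not settle which applies; the schedule puts screening and execution in different months but does not mention a second pre-treatment reading. Outcome sulfhydride values may be slightly lower in all arms because they follow a swab. The sample size and the visits do not change.

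**Limit.** The reordering corrects the within-group baseline only. It does not remove any influence of the pre-treatment swab on the between-group contrast, nor regression to the mean.
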